## Abstract

**Background:**

Anorexia nervosa (AN) is a debilitating psychiatric disorder associated with a wide array of negative health complications and psychiatric comorbidity. Existing evidence for AN treatment in adults is weak, and no empirically supported treatment has been reliably established. The primary objective of this study is to gain knowledge about the effectiveness of enhanced cognitive behavioral therapy (CBT-E) for anorexia nervosa delivered in a public hospital setting. Baseline predictors of treatment outcome and dropout are studied. Furthermore, there will be collected blood and stool samples for a general biobank to be able to initiate research on possible pathophysiological mechanisms underlying AN.

**Methods:**

The study will assess the potency of outpatient CBT-E in a sample of patients suffering from AN (age >16) admitted to the Section for Eating Disorders at the Department for Psychosomatic Medicine, Haukeland University Hospital in Bergen, Norway. The study has a longitudinal design with five main assessment time points: before treatment, at 3 months, at the end of treatment, at 20 weeks, and at 12 months follow-up including biobank samples. A control group without an eating disorder will also be recruited.

**Discussion:**

Treatment research in a public hospital setting is important for gaining knowledge about the transportability of treatments evaluated in research clinics into ordinary clinical practice. Furthermore, biological material from the thoroughly described patient cohort will serve as a basis for further research on the pathophysiological mechanisms in AN.

**Trial registration:**

ClinicalTrials.gov Identifier: NCT02745067. Registered 14 April 2016. ﻿

## Background

### General overview

Anorexia nervosa (AN) is a debilitating psychiatric disorder characterized by abnormal eating behaviors, severe weight loss, intense fear of gaining weight or becoming fat (despite being underweight), and having a disturbed body image [1]. AN is associated with a wide array of negative health complications that cause suffering or even premature death in affected patients, as well as posing a heavy burden on public health-care services [2–4]. Psychiatric comorbidity is common with AN, with depression and anxiety disorders being the most prevalent [5], and there is a significantly increased risk of death by suicide [6]. The risk of mortality is reportedly sixfold higher in patients suffering from AN than in the general population [7], and a meta-analysis of 3006 patients admitted to hospital due to AN found that the 10-year mortality rate was 5.9 % [8].

Successfully treating AN is challenging. This condition is associated with a poor prognosis, including high rates of enduring illness and treatment dropout [9, 10]. Previous studies suggest that less than half of AN patients recover completely from the disorder. A substantial proportion of AN patients develop severe and enduring AN [11]. The adverse effects of AN combined with the high risk of severe and enduring AN indicate a substantial need for effective treatment options.

According to the two most widely influential treatment guidelines from the National Institute for Health and Clinical Excellence (NICE) [12] and the American Psychiatric Association [5], existing evidence for AN treatment in adults is weak, while Family-Based Treatment (FBT) is recommended for youths. The highest level of evidence for adult AN treatment in the NICE-guidelines is grade C, based on a consensus among experts rather than actual effectiveness as demonstrated in well-conducted clinical studies. The clinical consensus indicated that focal psychodynamic therapy, cognitive behavioral therapy (CBT), interpersonal psychotherapy, and cognitive analytic therapy are equally beneficial [5, 12].

The scarcity of research on treatments for AN might be partially due to several factors that complicate the ability to investigate this condition in well-designed studies, including its low prevalence, severity of medical complications, very high dropout rates, and the extended treatment duration required to successfully treat the disorder [13]. Halmi and colleagues [13] argued that it is necessary to study and address treatment dropout and refusal before further large randomized controlled trials (RCTs) of AN are initiated [13]. Fassino and colleagues argued [9] that avoiding treatment dropout is important, since those who drop out often have worse long-term prognoses, tend to be referred again at a later time when their problems are more severe, and their illness is more chronic and more prone to relapse [9]. Moreover, dropping out is expensive to society.

New treatment guidelines for AN are under development in Norway. There are five regional eating-disorder units in Norway, and they each apply somewhat different treatment approaches for AN, which reflects the difficulty of reaching an evidence-based consensus for treatment recommendations. Thus, there is a need for studies evaluating the treatment responses for different psychological AN treatments. Likewise, knowledge about which patients benefit from particular treatments, and predictors and reasons for treatment dropout is important for improving treatments, preventing treatment dropout, and making more-informed choices when tailoring treatments for individual AN patients.

### Evaluation of outpatient CBT-E as a standard treatment for adult AN patients in a public hospital

As discussed above, the existing evidence for AN treatment is weak and no empirically supported treatment has been reliably established for adults with AN [12, 14, 15]. There is therefore a need to document the effects of existing treatments for AN.

CBT-BN is currently the leading evidence-based treatment for bulimia nervosa (BN) [12]. The enhanced version of this treatment (CBT-E), developed during the last decade, has taken a “transdiagnostic approach” to eating disorders [16]. The CBT-E model is based on the assumption that common cognitive mechanisms, such as overevaluation of body shape and weight, underlie all eating disorders [17].

Fairburn and colleagues [18] investigated the outcomes in 99 adult patients with AN resulting from treatment with CBT-E [18]. The results showed that two-thirds of the patients completed the 40-week treatment intervention, with outcomes of clinically significant weight gains and significant reductions in eating-disorder pathology. The results further demonstrated that overall changes were well maintained after a 60-week follow-up period [18]. These findings are in line with another study suggesting that CBT-E is an effective treatment for adolescents with AN [19]. A recent study from Germany (the ANTOP study) compared CBT-E and focal psychodynamic therapy with optimized treatment as usual, and found significant weight gains in all treatment groups, but no significant differences in the effects on body mass index (BMI) and eating-disorder pathology between the treatment approaches [20]. These studies suggest that CBT-E could be a useful treatment approach for adult AN.

Our study will evaluate the use of CBT-E as a standard treatment for AN in the regional eating-disorder unit of a public hospital. Based on a survey of eating-disorder professionals, Wallace and von Ranson [21] argued that there is a disconnection between research and practice in eating-disorder treatment [21]. They further claimed that when empirically supported interventions are implemented in practice, they tend to become embedded within more eclectic treatment approaches and are not used in their original forms as evaluated in research clinics. Our study is one of the first to aim at using the CBT-E protocol as a standard noneclectic treatment for all AN patients able to undergo psychotherapy in a regional eating-disorder unit at a public hospital.

### Baseline predictors of treatment outcome and dropout, and dropout analysis

High dropout rates have been regarded as a major problem in AN treatment research since they make it difficult to conduct RCTs. This further implies that a relatively large proportion of patients are not able to benefit from current AN treatments. Few previous studies have investigated the characteristics of those patients who do not benefit from AN treatment and their reported reasons for dropping out. Moreover, the predictors of treatment outcome and dropout have to our knowledge not been studied in CBT-E treatment for AN. Such knowledge could act as an important guide for identifying those patients who might need other treatment approaches or how treatments may be improved or tailored for different subgroups of patients.

The rate of treatment dropout is generally reported to vary between 29 % to 73 % in outpatient samples of AN patients [9]. Dropout rates of 36 % and 37 % have been reported for CBT-E treatments of AN [18, 19]. The ANTOP study found dropout rates of 19 % for CBT-E and 34 % for focal dynamic therapy in AN patients [20], suggesting that dropout rates from CBT-E are not higher than those of other treatments for AN, but that they are still significant.

Even though dropout is a major problem with AN treatments in general, and knowledge about the predictors and reasons for dropping out are important in planning and improving interventions, the findings of the few studies investigating this have been ambiguous, and they have mainly focused on personality factors and aspects of the eating disorder [9]. One study examining predictors of dropping out from CBT-E treatment among a mixed group of eating-disorder patients found that treatment dropout was predicted by a history of very low weight, avoidance of affect, and a longer time on waiting lists before starting treatment [22]. Surprisingly few studies have investigated how sociodemographic factors influence treatment outcomes, with one recent review concluding that such data are more or less nonexistent [23].

In terms of clinical experiences of AN, higher symptom severity, longer duration of illness, lower baseline BMI, higher number of prior treatment attempts and dropouts, higher age and degree of psychiatric symptoms and comorbidity are often considered to make treatment and recovery more difficult. The present study will examine these baseline characteristics as well as sociodemographic factors as predictors of treatment outcomes and dropout. The findings should constitute new and valuable clinical evidence for guiding which groups of patients are most likely to benefit from CBT-E treatment for AN.

Subjective experiences of the patients are also important when evaluating the reasons for treatment dropout and the suitability of a treatment. Possible reasons for treatment dropout include (1) lack of motivation, (2) feeling able to manage on your own and not needing further treatment, (3) dissatisfaction with the treatment model, (4) not feeling capable of doing the tasks required, (5) lack of good alliance with the therapist, (6) not experiencing satisfactory results from the treatment, and (7) having other competing activities, work difficulties, family problems, or other health problems. To our knowledge there are no previous reports on patient evaluations of the reasons for the premature termination of AN treatment.

### Process factors, therapeutic alliance, and early patient engagement in treatment as predictors of outcome and dropout

Most previous studies of predictors of treatment outcome and dropout from AN treatment have focused on characteristics of the patients. Therefore, the factors related to the treatment process itself warrant investigation [22].

An early response to treatment might reflect patient engagement in therapy and readiness to change, which might be predictive of the eventual treatment outcome or dropout [24]. In CBT-E [17], patient adherence to the behavioral goals of the treatment during the first 4 weeks is suggested to be predictive of the overall treatment outcome; however, this is a hypothesis that requires further scientifically testing. Two studies of different treatments of AN found that adequate weight gain over the first 4 weeks significantly predicted retention in the treatment program [25, 26]. The time before starting to regain weight during treatment and the rate of weight gain might be strong predictors of treatment outcome and retention. In addition, a reduction of binge-eating episodes and vomiting during the first weeks of treatment and the establishment of regular meals seem to be significant prognostic factors [17, 24, 27]. The present study will acquire weekly data on BMI, number of days with regular eating, and the numbers of weekly binge-eating and purging episodes. This information might be useful for clarifying to what extent an early change in CBT-E treatment is predictive of the overall treatment outcome.

The therapeutic alliance is one of the factors found to be related to symptom changes and treatment outcome in psychological treatment research [28, 29]. Establishing an early strong alliance in the treatment of AN has traditionally been considered difficult because these patients often deny the presence of the disorder. Further, AN patients usually have severely reduced cognitive function due to malnutrition, and most patients are ambivalent to treatment [30]. However, while some studies in contrary to this assumptions have found quite a strong therapeutic alliance in treatments for AN [31, 32], few studies have examined the nature of the relationship between therapeutic alliance and symptom change in AN [31–34]. One study found the therapeutic alliance in CBT treatment for AN to be relatively strong, but interestingly weight gain was found to predict a stronger alliance while a strong early alliance did not predict weight gain [31].

### Psychiatric comorbidity

Psychiatric comorbidity is common in AN, with depression and anxiety disorders being the most prevalent conditions. The American Psychiatric Association has reported lifetime prevalence rates for major depressive disorder in individuals with eating disorders of between 50 % and 75 % [5]. Previous studies that have compared comorbidity between AN and mood disorders have produced widely varying findings, with lifetime prevalence rates of between 31 % and 88.9 % [35]. However, these studies have not always addressed the difference between psychological symptoms related to AN and comorbid psychiatric disorders. This is particularly interesting because there is a clinical consensus that symptoms of depression and anxiety with AN are partially linked to malnutrition, and are symptoms of starvation [5]. The widely cited starvation study conducted by Keys and colleagues in 1950 indicated that malnutrition causes anxiety and depressive symptoms [36]. However, few subsequent studies have shed further light on the link between malnutrition and these psychological symptoms [37]. A review of seven studies investigating the relationship between BMI and depression/anxiety symptoms found general decreases in depression and anxiety symptoms associated with weight gain after treatment [37]. From this perspective, depression and anxiety represent interesting secondary outcome measures in the treatment of AN.

### Physical activity

High-level physical activity, excessive exercise, and compulsive exercise play a central role in the eating disorder pathology of many patients with AN, and these might have been part of the pathogenesis of their disorder [38]. Several terms are used to describe the nature of physical activity that is considered a maintaining factor in AN, some focusing on the quantitative dimension of physical activity while others are related to the more-subjective experience of the compulsiveness of physical activity [39]. This compulsiveness has been suggested to be more connected to eating disorders than the excessiveness of the exercising itself [40]. Further, the regulation of negative emotions and compulsivity can maintain excessive levels of physical activity [41]. Dalle Grave and colleagues [39] found that compulsive exercise was performed by 80 % of patients with restrictive AN and by 43.3 % of patients with purging AN.

Excessive exercise and high-level physical activity have not been widely studied in AN, and there are neither established terminologies nor criteria for their use in definitions or measurements [39, 42]. Most studies rely on self-report measures of physical activity, and so new studies using objective measures are warranted [42]. Alberti and colleagues [43] compared a self-report measure and an objective measure of physical activity in AN patients, which revealed significant underreporting of physical activity level in this population.

There is a need for more knowledge about the impact of high-level physical activity and compulsive exercise on the treatment outcome and maintenance in AN. Dalle Grave and colleagues [39] found that a lower amount of exercise during the preceding 4 weeks predicted an improved eating-disorder symptomatology at the treatment follow-up. Two other studies found excessive exercise to be related to longer treatment duration [44], a more-enduring eating-disorder pattern, and early relapse after treatment [45]. These studies indicate that excessive exercise/high level physical activity/compulsive exercise is important to address and manage in the treatment of AN [46].

### Biobank

Despite the rapidly increasing knowledge about several aspects of the pathophysiology of AN, there is still no unifying theory for its etiology. AN is a multifactorial disease, and environmental, social, psychological, genetic, bacterial, and endocrine factors are thought to influence its pathophysiology [47, 48]. Acknowledging this, the present study will establish a biobank (blood and stool samples) to be able to initiate research on possible pathophysiological mechanisms that play a role in the pathophysiology of AN. Specifically, we will focus on the gut microbiota as well as genetic and biochemical/immunological markers. The longitudinal design of this study and the inclusion of a healthy control group are significant strengths that will contribute to a better understanding of AN pathophysiology, which could have implications for treatment efficacy.

## Research questions

Based on the literature discussed above, this study will address and attempt to answer the following main research questions:

**Research question 1: Evaluation of outpatient CBT-E as a standard treatment for AN**

Do adult AN patients provided with CBT-E treatment in a Norwegian outpatient setting show favorable pre-post changes, and are these sustained at 12 months after ending treatment? We expect changes to occur in the following areas: weight gain and eating-disorder pathology, depressive symptoms and depression, anxiety, general psychological impairment, and health-related quality of life.

**Research question 2: Baseline predictors of treatment outcome and dropout, and dropout analysis**
Do baseline BMI, duration of illness, number of prior treatment attempts, number of prior dropouts, time on waiting lists, socioeconomic status, work status, social network support, level of depression, anxiety, presence of other psychiatric diagnoses (as assessed using the Mini International Neuropsychiatric Interview [MINI]), and general psychological symptomatology predict treatment outcome or dropout?Which factors do patients who drop out from CBT-E treatment report as reasons for ending treatment prematurely? This will be an explorative study and we would expect patients who drop out to report different reasons when interviewed, such as lack of motivation, feeling satisfied with their current situation, fear of change, dislike of the treatment method, difficulties in performing the tasks required, poor relationship with the therapist, and presence of other illnesses or other competing activities.

**Research question 3: Therapeutic alliance, and early patient engagement in treatment as predictors of pre-post outcome and dropout**

Do early (4 weeks) behavioral changes, adherence to treatment, and therapeutic alliances predict the pre-post outcome and dropout in CBT-E treatment for AN?

**Research question 4:** To what extent is there a link between weight and depressive symptoms; does change in BMI predict change in depressive symptoms?

**Research question 5: Physical activity**
Does the physical activity level as measured by accelerometers differ between AN patients and matched normal-weight healthy controls without an eating disorder?Is there a change in excessive or compulsive exercising (pretreatment versus posttreatment)?Does high-level physical activity and compulsive exercise at baseline predict a worse treatment outcome as determined by BMI and the EDE-Q and Clinical Impairment Assessment Questionnaire (CIA)?Does a higher level of physical activity at the end of treatment predict relapse or higher scores on EDE-Q at 12 months after ending treatment?

## Methods/Design

### Study design

The current project is an open, longitudinal treatment study undertaken in an ordinary clinical setting at a regional eating-disorder unit (Section for Eating Disorders, SED). All patients will receive a minimum of 40 sessions of outpatient CBT-E that cover the different treatment sessions described in the CBT-E manual for underweight patients [17], which is the standard treatment for AN at our unit. A control group without eating disorders will also be recruited.

### Patient sample

All patients who agree to receive treatment for AN at the SED will be asked to participate in the study. Patients are referred to the clinic by general practitioners and secondary (specialist) health-care services. Written informed consent will be obtained after the patients have received written and oral descriptions about the study. During the past 2 years, 96 AN patients were offered treatment at the SED. We aim to include 100 patients in the current study. Analyses of statistical power showed that the proposed sample sizes in the different studies are sufficient.

The study will include patients aged >16 years who are suffering from AN, as diagnosed based on the DSM-5 (Diagnostic and Statistical Manual of Mental Disorders, Fifth Edition) [1] and confirmed with a clinical examination. Patients offered treatment at the SED have either at least one unsuccessful treatment attempt in a secondary health-care service unit or severe AN that is evaluated as not manageable in a secondary health-care service unit. Participation in the study will be offered to patients younger than 18 years if they do not fulfill the criteria for receiving FBT for AN [49]. Patients will be excluded from participation if it is deemed unsafe to manage them on an outpatient basis or have psychiatric comorbidity (as evaluated with MINI [50]) that precludes a focused eating-disorder treatment, such as psychosis or drug abuse. Patients who are not available to participate during the requested treatment period will also be excluded.

In line with clinical practice, patients will be withdrawn from outpatient treatment if they are unable to participate actively in the treatment program according to the judgement of the clinician, based on not attending sessions (more than three consecutive treatment sessions without giving notice) or not engaging in using the treatment tools (e.g. not self-monitoring).

Treatment at the SED is offered in a stepped care model, whereby patients participating fully in outpatient treatment but still not achieving the necessary changes will be offered a more-intensive treatment option (Intensive CBT-E) as inpatients or in day care. These patients will be included as a separate group in the analyses.

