### Control group

A healthy control group (consisting of 30-35 persons) will be recruited through advertisements and matched to the patient group in terms of age, gender, and length of education. In order to control for longitudinal changes, the control group will be tested twice, with an interval of 1 year. The control group will provide activity measures, blood and stool samples, and complete the EDE-Q.

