#### Power analyses

All power analyses were conducted with G*Power software (version 3.1.7) [75]. A large effect size is expected for the study treatments (*d* = 0.8). Alpha was set to 0.05 and the power was set to 0.80. The coefficient for the correlation between measurement points was set to 0.50. The results showed that 12 subjects would be needed to detect a significant effect of time. In terms of dropouts, Pr(Y = 1∣X = 1) H0 (which signifies the probability of dropping out when all predictors/covariates are set to their mean values) is set to 0.25. For a two-tailed odds ratio of 2.0, an alpha of 0.05, and a power of 0.80, a sample size of 100 is needed when the R^2^ values of other predictors are set to 0. Linear regression of the treatment outcome with an expected regression coefficient of *d* = 0.20 (two-tailed) and with alpha set to 0.05 and the power set to 0.80 indicated that 81 subjects are needed.

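### The blanket statement that sample sizes are sufficient goes beyond the three power calculations reported: relapse and the patient-control comparison were not sized, and relapse would probably fall short of 80% power at an odds ratio of 2.0

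*Protocol article*

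**What the plan says.** Under Patient sample, the article gives the target, "We aim to include 100 patients in the current study", and follows it with the conclusion "Analyses of statistical power showed that the proposed sample sizes in the different studies are sufficient".

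Under Power analyses, the common settings are "Alpha was set to 0.05 and the power was set to 0.80". Three results follow:
- Time effect, with d = 0.8 and a correlation of 0.50 between measurements: "The results showed that 12 subjects would be needed to detect a significant effect of time".
- Dropout by logistic regression, with a probability of 0.25 at the mean of the predictors: "For a two-tailed odds ratio of 2.0, an alpha of 0.05, and a power of 0.80, a sample size of 100 is needed".
- Linear regression of treatment outcome: 81 patients.

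Research question 5 has four parts: patients versus controls on accelerometry; pre-post change in exercise; baseline activity as a predictor of outcome; and, last, "Does a higher level of physical activity at the end of treatment predict relapse or higher scores on EDE-Q at 12 months" after treatment ends. The Control group section fixes a separate sample: "A healthy control group (consisting of 30-35 persons) will be recruited through advertisements".

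On how many patients might be at risk of relapse, the only relevant statement is background: "Previous studies suggest that less than half of AN patients recover completely from the disorder".

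**The concern.** The sufficiency sentence covers every study in the project, but the section it rests on has no two-group calculation and none with relapse as the outcome. For relapse this is more than an unreported calculation. The plan's one standard for a binary outcome takes the full 100 patients to reach 80% power, and relapse has a smaller denominator because a patient must first have remitted.

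If the sentence stands, a null result for relapse would come from a sample described in advance as adequate. It could then be taken as evidence that activity at end of treatment does not matter, although the test may have had little better than an even chance of detecting a doubling of the odds.

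**Working it through.** **1. Which parts of research question 5 are sized**

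| Part | Type of analysis | Covered under Power analyses? |
|---|---|---|
| Patients vs controls, accelerometry | Two-group comparison | No |
| Pre-post change in exercise | Time effect | Yes, by type (12) |
| Baseline activity and outcome | Linear regression | Yes, by type (81) |
| End-of-treatment activity and 12-month EDE-Q | Linear regression | Yes, by type (81) |
| End-of-treatment activity and relapse | Binary outcome | No; the only logistic calculation is for dropout |

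**2. The plan's own figure for a binary outcome**

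Inputs from Power analyses: OR 2.0 (taken per standard deviation of a normal predictor), probability 0.25, two-sided alpha 0.05, power 0.80. The Hsieh approximation gives

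n = (1.960 + 0.842)² / [p(1−p)(ln OR)²] = 7.849 / (0.1875 × 0.4805) = 87.1, so 88.

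The Demidenko versions give 90-93 and the plain Wald version 108. These bracket the stated 100, and power at 100 is 77-85% across methods (81-83% by simulation). The dropout figure is therefore reasonable and is not in dispute.

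**3. Relapse, borrowing OR 2.0**

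Assumptions, none of them planning inputs in the article:
- At risk: 50 of 100, the upper end of the Background statement on complete recovery; or 37, which is 50 × 0.75 = 37.5 if the 25% used for dropout is also removed.
- Relapse among those at risk: 20-50%.

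Hsieh power is Φ(√[n p(1−p)] × ln OR − 1.960). With n = 50 and p = 0.25: √9.375 = 3.062; 3.062 × 0.6931 = 2.122; 2.122 − 1.960 = 0.162; Φ(0.162) = 56%.

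| At risk | Method | Relapse 20% | Relapse 25% | Relapse 50% |
|---|---|---|---|---|
| 50 | Hsieh | 50% | 56% | 69% |
| 50 | Wald test, simulated | 43% | 49% | 58% |
| 50 | Likelihood ratio, simulated | 49% | 54% | 63% |
| 37 | Hsieh | 39% | 45% | 56% |
| 37 | Wald test, simulated | 30% | 35% | 44% |
| 37 | Likelihood ratio, simulated | 39% | 44% | 52% |

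Simulated values move by about a percentage point between runs; across the runs made, the lowest for 50 at risk was about 42%. Every cell is below 80%.

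Turned round, 80% power at a 25% relapse rate needs 88 (Hsieh) to 108 (Wald) remitted patients. At the most favourable rate, 50%, Hsieh still needs 7.849 / (0.25 × 0.4805) = 65.3, so 66, which is more than half of 100.

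**4. Patients versus controls**

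Two-sample t test, two-sided alpha 0.05:

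| Groups | d at 80% power | Power at d = 0.3 | at d = 0.5 | at d = 0.8 |
|---|---|---|---|---|
| 100 vs 30 | 0.59 | 30% | 66% | 97% |
| 100 vs 35 | 0.55 | 33% | 72% | 98% |

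**5. The continuous alternative**

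The stated 81 reproduces exactly for one predictor with f² = 0.10. On that basis power is 88% with 100 patients and 70% with 63 (100 less 37%, the higher of the two CBT-E dropout rates of 36% and 37% that the Background cites). This analysis does not need remission, so it keeps more patients than the relapse test.

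**The case against.** The strongest reply is that the relapse figures are the reviewer's and not the plan's. That is correct. The article gives OR 2.0 and the 0.25 rate for dropout only, and states no relapse rate, relapse odds ratio or remission share. A reader might say that low relapse power follows from the plan's own inputs. It does not: it follows from borrowed and assumed ones. The Background statement concerns complete recovery in earlier studies, and a broader definition of response, which an article may leave to the full protocol or analysis plan, would put more patients at risk. With 67 at risk, Hsieh power is 62-81%. A larger effect also changes the answer: OR 3 with 50 at risk gives roughly 85%. Taking a further 25% off to reach 37 may count dropout twice, because the recovery statement is not limited to completers.

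Three stronger readings are not supported:
- That nothing in research question 5 is sized. The pre-post, baseline-predictor and 12-month EDE-Q parts are of types that the Power analyses section does size.
- That the control group is too small. At d = 0.8, the only d for a mean difference in the article (given for treatment), power is 97-98%. The comparison is uncalculated, not shown to be insufficient.
- That the association would be diluted because never-remitted patients count as non-relapsers. The article states no such analysis rule.

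It is also fair that relapse is one of two alternatives in the last part of the last research question, and that the other, EDE-Q, is the primary outcome measure. This limits the consequence, and it also makes the remedy easy.

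**Conclusion.** The point holds in a limited form. The sufficiency statement is wider than the calculations behind it, because the patient-control comparison and relapse have none. This rests on the text alone.

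The size of the relapse shortfall is conditional. At OR 2.0, with at most about half of 100 patients remitted and 20-50% of them relapsing, power is about 42-69% with 50 at risk and 30-56% with 37, against the plan's 80%. A reasonable single figure is about 55%, for 50 at risk and a 25% relapse rate. The claim for relapse is therefore unsupported, and unlikely to hold at the effect size the plan chose for its other binary outcome. It is not proven false for every definition of relapse or every effect size. The three reported calculations are not challenged here, and for controls the gap is one of disclosure.

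**What to change.** - Under Patient sample, limit the sufficiency sentence to the analyses sized under Power analyses: time effect, dropout and linear regression of outcome.
- State that relapse was not sized and that at OR 2.0 its power is expected to be below 80% (about 55% with 50 at risk and a 25% relapse rate, both labelled as assumptions).
- For the last part of research question 5, make the continuous 12-month EDE-Q, which the question already names, the lead outcome. Report relapse as exploratory, among patients in remission at end of treatment, with a confidence interval so that a null result is not read as no association.
- State that 100 patients versus 30-35 controls gives 80% power for a standardised difference of about 0.55-0.59.

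The cost is a few sentences and a less favourable statement about relapse. No extra patients, visits or measurements are needed.
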